### Outcome measures

#### Primary outcome measure

The primary outcome is large-for-gestational age birth weight (LGA, defined as birth weight > 90th centile, using the Dutch Perined reference charts, according to Hoftiezer [28]), retracted from the eCRF.

#### Secondary outcomes

Secondary outcomes will include all outcomes defined in the core outcome set for studies of gestational diabetes mellitus prevention and treatment; Table 2 [29].

**Table 2 Tab2:** Secondary outcome

Gestational age at time of inclusion	In weeks and days
Adherence to the intervention	Did participants complete treatment according to allocation group until delivery: yes/no
Hypertensive disorders of pregnancy	Pregnancy induced hypertension, Pre-eclampsia (defined as by the ISSHP(30)), HELLP (Hemolysis, Elevated Liver enzymes, Low Platelets)
Requirement and type of pharmacological therapy for hyperglycaemia	If yes, oral medication, insulin, other
Gestational weight gain	In kilograms
Mode of birth	Spontaneous, assisted vaginal, caesarean (if instrumental: fetal distress or failure to progress)
Gestational age at birth	In weeks and days
Birth weight	In grams
Small for gestational age	Defined as birth weight < 10th centile, using the Dutch Perined reference charts, according to Hoftiezer(28)
Preterm birth	< 37 weeks (0 days) gestational age
Neonatal glucose postpartum	As a continuous outcome measure and as dichotomous outcome: moderate, glucose < 2.6 mmol/l; severe, glucose < 2.0 mmol/l(6)
Neonatal intravenous glucose	Yes/no
Stillbirth	Yes/no
Neonatal death	Yes/no
Secondary outcomes we will report in addition to the core outcome set:	
Macrosomia	Birth weight > 4500 g
Reason for preterm birth	Medically indicated or spontaneous contractions and/or spontaneous rupture of membranes
Onset of labour	Spontaneous, planned Caesarean section, induction of labour
Method(s) of induction of labour	Foley catheter/mechanical, prostaglandines, amniotomy, oxytocin, other (more than one optional)
Postpartum hemorrhage	> 1000 ml blood loss
Puerperal sepsis requiring antibiotics	Yes/no
Maternal admission postpartum	Yes/no, if yes: duration in days
1-min Apgar score, 5-min Apgar score, 10-min Apgar score	
Shoulder dystocia	Yes/no
Birth injury	i.e. fractures, nerve palsy
Cord blood C peptide	In a subset, where available
Neonatal intensive care/medium care admission	Yes/no, if yes: duration in days.
Hyperbilirubinemia	Yes/no
Respiratory support > 24 h	Yes/no
Neonatal encephalopathy	Yes/no
Other:	serious health outcomes up to the time of primary hospital discharge assessed from patient medical records(31)

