#### Intensive GDM treatment

Participants randomized to intensive treatment will be counselled on the diagnosis of GDM and conventional GDM treatment will be initiated. Treatment will comply with the national guideline for GDM [22] and will include:

Self-monitoring of blood glucose (target values: fasting *≤* 5.3, 1-hour postprandial *≤* 7.8 and/or *≤* 6.7mmol/l), or target values according to local protocol (e.g. 1.5-hour postprandial < 7 mmol/l). The recommended frequency for blood glucose measurements is (initially) daily, four times a day.Dietary recommendations [23].Pharmacotherapy for those unable to achieve euglycemia with dietary intervention alone: guidelines in the Netherlands suggest insulin as a first choice; oral antihyperglycemic agents are optional at the clinician’s discretion [6].

Mode and timing of delivery, postpartum advice, and postpartum screening for neonatal hypoglycaemia will be conducted based on the NVOG guideline for GDM and/or local protocol. Additional ultrasounds and induction of labor could be part of the intervention, but are not mandatory according to national guidance, which does recommend induction of labor before 39 weeks gestational age in case of GDM requiring medication. Postpartum recommendations after GDM include annual visits at the general practitioner to rule out diabetes type 2. Furthermore, in subsequent pregnancies after GDM, early OGTT screening is offered at 16 weeks, in addition to routine screening at 24–28 weeks.

In addition to the indications in standard care, postpartum screening for neonatal hypoglycaemia is recommended only for infants of GDM mothers treated with insulin or oral antihyperglycemic agents. Diet controlled GDM is not considered a routine indication for neonatal hypoglycemia screening [6].

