#### Normal obstetric care

Participants randomized to normal obstetric care will receive maternity care by their usual care provider (midwife or obstetrician, as appropriate), according to common practice, local protocol and/or national guidelines [24, 25] for the duration of the pregnancy, birth and postpartum period. This includes that advice regarding future pregnancies, glucose testing and neonatal screening for hypoglycemia will only be offered in case of risk factors including macrosomia or small for gestational age. In contrast to intensive GDM care, in future pregnancies, early screening for GDM will not be advised, and yearly checkups at the general practitioner to rule out type 2 diabetes will not be indicated.

For participants randomized to normal obstetric care, who have been randomized early in pregnancy (16–20 weeks) and who have been tested because of a prior pregnancy complicated by GDM, a repeat OGTT will be carried out at 24–28 weeks of gestational age as part of routine antenatal care. Alternatively, a clinical indication may arise to repeat the OGTT later in pregnancy, for instance because of clinical symptoms. Among participants allocated to normal obstetric care, when glucose values are normal or discordant, normal obstetric care will be continued. Glucose values exceeding the discordant results (fasting *≥* 7.0 OR 2-hour post load glucose value *≥* 8.5 mmol/l) will result in initiation of GDM treatment (see Figs. 1 and 2), which will result in appropriate recommendations for future pregnancies, postnatal screening for diabetes type 2 and may include neonatal hypoglycemia screening.

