#### Planned analyses

Baseline characteristics will be presented as frequencies and percentages in each group, or as averages (mean or median) with standard deviations or interquartile ranges as appropriate. The primary outcome will be evaluated by estimating the relative risk between both treatment arms. Analyses will be conducted in both the intention-to-treat and per protocol population for the primary outcome.

Relative risks will be estimated for categorical outcomes, with 95% confidence intervals, and χ2 tests for significance. Fisher’s exact test will be used for sparse events where assumptions of the χ2 test are not met. Continuous data will be described as means with standard deviation if normally distributed, or medians with interquartile ranges when not normally distributed; tests for significance are t-tests or Mann-Whitney U tests, respectively. The Hodges-Lehman estimator will be used to calculate the confidence interval for the difference in medians.

Individuals who were randomized to normal obstetric care but for unknown reasons received treatment they will be excluded from the per protocol analysis. If the treatment followed an abnormal repeat OGTT they will remain in the per protocol analysis. Individuals who were randomized to GDM treatment but for unknown reasons never received treatment will be excluded from the per protocol analysis. If, per example, they did not receive treatment because of preterm birth they will remain in the per protocol analysis.

Subgroup analyses will be performed for BMI (under or above 30 kg/m2), early or late GDM (before or after 24 weeks) and according to the result of the OGTT (abnormal fasting result, abnormal postprandial result, or both).

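### Neonatal glucose is to be compared between arms, but the care rules trigger testing differently by arm, so the comparison can be biased in either direction

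*Protocol article*

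**What the plan says.** **Outcome.** Table 2 (Secondary outcomes) lists neonatal glucose within the core outcome set: "As a continuous outcome measure and as dichotomous outcome: moderate, glucose < 2.6 mmol/l", with a severe category below 2.0 mmol/l. The row does not mark it as available only in a subset, as the cord C-peptide row does.

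**Testing, intensive arm.** The section on intensive GDM treatment says that "postpartum screening for neonatal hypoglycaemia will be conducted based on the NVOG guideline for GDM and/or local protocol". It then adds one trigger to those of standard care: "postpartum screening for neonatal hypoglycaemia is recommended only for infants of GDM mothers treated with insulin or oral antihyperglycemic agents". It limits that trigger: "Diet controlled GDM is not considered a routine indication for neonatal hypoglycemia screening".

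**Testing, control arm.** Under Normal obstetric care, "neonatal screening for hypoglycemia will only be offered in case of risk factors including macrosomia or small for gestational age". Control women who start GDM treatment after a repeat test above the discordant range receive care that "may include neonatal hypoglycemia screening".

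**Analysis.** Planned analyses states: "Relative risks will be estimated for categorical outcomes, with 95% confidence intervals", with χ² or Fisher tests, and t-tests or Mann-Whitney tests for continuous data. The Cost-effectiveness section takes the perinatal outcomes as effect measures.

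**The concern.** A between-arm test on glucose reads as a treatment effect only if infants in both arms are measured in the same way. Here the rule that decides who is measured contains a trigger, maternal medication, that belongs almost entirely to one arm.

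Two distortions follow, and they point in opposite directions. If every randomised infant is in the denominator and untested infants count as no event, more testing in an arm produces more detected cases. If only tested infants are analysed, the tested controls are mainly infants with a risk factor, while the tested intensive-arm infants also include those whose only trigger is maternal medication. The second problem also affects the comparison of continuous glucose values.

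At stake is a core-set outcome in a trial meant to weigh benefits, harms and costs of the 2013 criteria. A spurious signal could be reported as harm or benefit and could enter a cost-effectiveness ratio.

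**Working it through.** **The plan's own figure.** The article gives no number for neonatal hypoglycaemia. Its sample size supplies the arm size used below. For LGA 16% v 10%, two-sided 5%, 80% power, unpooled variance:

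(1.960 + 0.842)² × (0.16×0.84 + 0.10×0.90) / 0.06² = 489.2, so 490 per arm; 490/0.95 = 515.8, so 516 per arm and 1032 in total. This matches the article. About 490 per arm are evaluable.

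**Inputs.**
- From the Sample size section: LGA 16% in controls; 16% (no effect) or 10% (design effect) in the intensive arm.
- Assumed, because the article gives no figure: SGA 10%; LGA or SGA as the standard trigger; medication share m of 10–40%, independent of that trigger; the same true risk of glucose below 2.6 mmol/l in every infant of both arms.

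**Share tested.** Control: 0.16 + 0.10 = 0.26. Intensive: r + (1 − r)m, with r = 0.26 (no LGA effect) or r = 0.10 + 0.10 = 0.20 (design effect).

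**All infants in the denominator, untested counted as no event.** With equal true risk, the relative risk of detected cases is the ratio of the shares tested. The last two columns give the chance of a falsely significant excess in the intensive arm at a true risk of 20% and 490 infants per arm (nominal 2.5% in that direction).

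| m | Tested, no LGA effect | RR | Tested, design effect | RR | Chance, no LGA effect | Chance, design effect |
|---|---|---|---|---|---|---|
| 10% | 33.4% | 1.28 | 28% | 1.08 | 16% | 5% |
| 20% | 40.8% | 1.57 | 36% | 1.38 | 46% | 25% |
| 30% | 48.2% | 1.85 | 44% | 1.69 | 76% | 60% |
| 40% | 55.6% | 2.14 | 52% | 2.00 | 92% | 86% |

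**Where the imbalance reverses.** With the design LGA effect, testing is equal when 0.20 + 0.80m = 0.26, so m = 0.06/0.80 = 7.5%. With no SGA trigger it is 0.06/0.90 = 6.7%. Below that share, fewer intensive-arm infants are tested.

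**Tested infants only.** Now let risk differ by infant: 25% with a risk factor and 10% otherwise (assumed), no treatment effect, m = 30%.
- Control, tested: 25%.
- Intensive, tested: (0.26×0.25 + 0.74×0.30×0.10)/0.482 = 0.0872/0.482 = 18.1%. RR = 0.181/0.25 = 0.72.
- Same infants over all randomised: 0.0872/(0.26×0.25) = 0.0872/0.065; RR = 1.34.

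The same data thus give apparent benefit or apparent harm according to the denominator. Over m = 10–40%, the tested-only RR runs from 0.87 to 0.68 and the all-infant RR from 1.11 to 1.46.

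**Control women treated after a repeat test.** If 10% of controls were treated and 30% of those medicated, control testing would rise from 26% to 0.26 + 0.74×0.10×0.30 = 28.2%. The gap narrows only slightly.

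**The case against.** **Size and direction are not documented.** A reader might infer that the care rules necessarily send more intensive-arm infants for testing and so produce false harm. The article does not support that. It gives no medication share, diet-controlled women add no routine trigger, and the imbalance reverses at low medication use if the LGA effect is achieved. A reader might also put the false relative risk at 1.8 to 2.6, from 20% standard indications, 20–40% medication and one flat risk: (0.20 + 0.80m)/0.20. Those inputs are assumed as well, and the flat risk matters most. With 25% risk in risk-factor infants and 10% in others, the same shares give 6.6–8.2% v 5.0%, a relative risk of 1.32–1.64. This objection stands in full.

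**The denominator belongs in the analysis plan.** This is fair, and its absence from an article is no fault. But it does not answer the point: both obvious denominators are distorted, because the unequal measurement comes from the care rules that the article itself states.

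**Missing effect data are imputed.** This applies to the economic evaluation. It helps little here, since control infants without a risk factor are not offered screening and few observed values would inform their imputation.

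**Intravenous glucose is no clean substitute.** This is also correct. In an open-label trial it largely follows a detected low glucose, so it inherits part of the same problem.

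**It is one secondary outcome among many.** True, and this limits the weight of the point.

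**Conclusion.** The point holds in a limited form. The documented facts are the arm-dependent testing triggers and the planned unadjusted between-arm tests. Together they mean that the comparison of neonatal glucose, continuous or at either cut-off, is confounded with testing, and no choice of denominator removes this.

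Direction and size are not documented. If untested infants count as no event, the illustrative relative risk under equal true risk is about 1.1 to 2.1 at 10–40% medication use. That rests on the assumed SGA rate, triggers, medication share and flat risk, and it shrinks if risk-factor infants carry higher risk. Below about 7.5% medication use with the full LGA effect, the imbalance reverses. A tested-only analysis can show false benefit. The plan does not establish that false harm will occur, only that the result could not be read as a treatment effect. The primary outcome and sample size are untouched.

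**What to change.** - Label the outcome as clinically detected neonatal hypoglycaemia.
- Report by arm the number of infants tested and the reason for testing.
- Present glucose values and the two threshold rates descriptively, and do not read between-arm p-values on them as a treatment effect. The core outcome is still reported.
- Do not use these rates as an effect measure in the economic evaluation without the same caveat.
- Report neonatal intravenous glucose, already listed as yes/no in Table 2, with all randomised infants as denominator, as the less testing-dependent comparison. State that it is rarer, hence less precise, and still partly subject to detection differences.

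The cost is wording in the outcome table and analysis section, plus recording the reason for testing if the case record form does not already do so. No change to the clinical screening rules is proposed.

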#### Baseline characteristics

Maternal baseline characteristics will be collected from the electronic patient file. We will provide a tabular presentation of the following baseline characteristics of both allocation groups, as well as the outcome variables: prepregnancy BMI (in kg/m^2^) and BMI at study entry, maternal age, parity, systolic and diastolic blood pressure at baseline and at study entry, intoxications (smoking, alcohol use), risk factors for GDM, reason for GDM screening, history of psychological problems, conception: spontaneous, fertility treatment (clomifene citrate, gonadotropins, IVF, ICSI), blood glucose concentrations at OGTT, gestational age at time of OGTT.

### Follow-up

To allow for long-term follow-up of both mothers and infants of the trial, all patients are asked for written consent to be approached for future studies with this purpose. However, follow up is not part of the current study, which ends at 6 weeks postpartum.

### Cost-effectiveness

The aim of the economic evaluation is to assess the incremental costs and the incremental health effects of intensive GDM treatment as compared to normal obstetric care in participants. Both a cost-effectiveness analysis (CEA) and a cost-utility analysis (CUA) will be performed from a societal and healthcare perspective according to Dutch guidelines [30] from diagnosis of GDM until 6 weeks postpartum. Because the time horizon of the economic evaluation is less than 12 months, discounting is not necessary.

Costs will be measured from a societal perspective using (web-based) questionnaires adapted from the iMTA Medical and Productivity Cost Questionnaires at a gestational age of 36 weeks and 6 weeks postpartum [26, 31]. Cost categories that will be included are: (1) healthcare costs (primary and secondary care, complementary cares and home care) (2) lost productivity costs (absenteeism from paid and unpaid work, and presentism) and (3) patient costs (informal care and other care services paid for by patients themselves). Valuation will be done according to Dutch costing guidelines [32]. For the valuation of health care utilization, lost productivity and informal care, Dutch standard costs will be used. Medication use will be valued using prices of the Royal Dutch Society for Pharmacy. Patient and family costs other than informal care will be valued using self-reported prices. For the valuation of absenteeism from paid work, the friction cost approach will be used.

The following effect measures will be included in the economic evaluation:LGA (birth weight > 90th percentile)Perinatal and maternal outcomes as stated in the section aboveQuality-Adjusted Life-Years (EuroQol (EQ-5D-5 L) with Dutch reference values) [31]

Missing cost and effect data will be imputed using multiple imputation according to the MICE algorithm developed by van Buuren [33]. Rubin’s rules will be used to pool the results from the different multiply imputed datasets. Bivariate regression analyses will be used to estimate cost and effect differences between intensive GDM treatment and normal obstetric care while adjusting for confounders if necessary. Incremental cost-effectiveness ratios (ICERs) will be calculated by dividing the difference in the mean total costs between the treatment groups by the difference in mean effect between the treatment groups. Bias-corrected and accelerated bootstrapping with 5000 replications will be used to estimate 95% confidence intervals around the cost differences and statistical uncertainty surrounding the ICERs. Uncertainty surrounding ICERs will be graphically presented on cost-effectiveness planes. Cost-effectiveness acceptability curves will also be estimated showing the probability that, in pregnant women with discordant OGTT results, intensive GDM treatment is cost-effective in comparison to normal obstetric care for a range of different ceiling ratios thereby showing decision uncertainty [34].

### Burden of treatment

We anticipate that the treated group will perceive their pregnancies as more intrusive and potentially harbor negative sentiments towards their pregnancies in contrast to women receiving standard obstetric care. With the Quality-Adjusted Life-Years (EuroQol (EQ-5D-5 L) with Dutch reference values) and the Social support questionnaire (SSQ, send 6 weeks post-partum) we will evaluate the differences between the treated and untreated group.

### Safety and monitoring

To safeguard the interests of the trial participants, a data safety monitoring board (DSMB) monitors the progress of the trial’s recruitment, and periodically assesses adverse events in order to safeguard against any treatment harm during the trial. A safety review is performed by an independent statistician and reviewed by the DSMB after the results are available for 50% of the patients. No interim analysis for efficacy is planned. This sample size was calculated to provide power to detect differences in a surrogate outcome, LGA, as opposed to safety outcomes. In the case of a statistically significant difference in LGA at an interim analysis, this will not be considered a reason to stop the study.

All serious adverse events (SAE) reported by participants or observed by the investigators or staff will be recorded. SAE definitions and standards for expedited reporting follow the international conference of harmonization good clinical practice (ICH GCP) guidelines on safety reporting [35]. All SAEs are reported to the accredited ethics committee that approved the protocol, according to the requirements of that committee.

### Sample size

In the planning phase of the study, we initially calculated a sample size of 2,520 participants (1,260 per group). This would generate sufficient power to detect a reduction of the primary outcome LGA from 14% in the group randomized to normal obstetric care to 9.8% in the group randomized to intensive GDM treatment among participants (alpha = 0.05, beta = 0.2). The assumed prevalence of LGA in the group randomized to normal obstetric care was based on the RESPECT study [36], in which a 5% prevalence of GDM was found in a cohort of patients from midwifery practices and secondary and tertiary hospitals in the Utrecht region of the Netherlands, according to the old (1999) criteria. The prevalence of LGA among women with GDM in the RESPECT cohort was 19%. Reasoning that the prevalence of LGA in women with a discordant OGTT results is likely to be lower than the mean for GDM patients, but higher than the general population (e.g. 10%) led us to an estimate of 14% in women without treatment. This estimate is confirmed by unpublished analyses within the RESPECT cohort, which found a 16% prevalence of LGA among discordant cases.

However, the subsequently published GEMS trial [13], which contained data on the LGA prevalence in discordant cases, triggered our power recalculation. The population in the sub-analyses of the GEMS trial with discordant test results was more similar to the population in the TANGO-DM than the previously used numbers of the RESPECT cohort. The prevalence of LGA in women with untreated mild hyperglycemia in the GEMS trial was 18.0% compared to 6.2% in the treated group. We therefore used a background incidence of 16% LGA (instead of the earlier 14%) in untreated women, to demonstrate or refute a reduction of LGA to 10% in participants who are treated and a 5% correction for women who are lost to follow up, we need 1032 participants (516 per group). The recalculation of the sample size was not informed by interim data of the TANGO-DM trial. The adjustment was approved by the Medical Research Ethics Committee of the Amsterdam UMC, and changed in the trial registration.

